#### Secondary Outcomes

Cardiovascular function indicators and body composition indicators will be assessed at T0, T1, and T2 in the community health center. Specific details have been published elsewhere [32]. Learning performance of health education knowledge will be evaluated using a comprehensive self-made questionnaire about the material at T0 and T1. Satisfaction and acceptability of this program were assessed at T1 for the intervention group through face-to-face interviews using 3-5 semistructured questions. The questions included: (1) “Do you find the program useful?” (2) “Is it worth your time?” and (3) “Would you feel confident recommending this program?” These questions were used in previous studies [37].

### Data Collection and Management

Health-related data will be collected and entered into the intelligent health promotion system at T0, T1, and T2. During the intervention, data for the intervention group were collected using WeChat (as shown in Figure 2). An independent data manager checked the database every week to ensure its integrity. Data lockup is being implemented to prevent any postmodification.

**Figure 2 figure2:**
[figure not shown]
Figure 2. Study flowchart. BP: blood pressure; BPMA: blood pressure monitoring adherence; DA: dietary adherence; EA: exercise adherence; MA: medicine adherence; PAT: physical activity time; WHBDIP: WeChat-based health behavioral digital intervention program.

### Statistical Analysis

All analyses will be performed using SPSS. Continuous variables will be presented as mean and SD values. Categorical variables will be expressed as numbers and percentages. Independent samples *t* tests and chi-square tests will be conducted to assess the significance of differences in baseline characteristics or outcomes between the control group and intervention group at 3 time points: before the start of the intervention, 12 weeks after the intervention, and 1 year after the program. Paired *t* tests and McNemar's test will be used to compare the differences in some outcomes before and after the 3-month intervention, as well as before the trial and after the end of the program. A *P* value of less than .05 will be considered statistically significant.

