**Methods:**

A 2-arm, parallel-group, and randomized trial design was used. Patients older than 60 years and with hypertension were randomly assigned to either the control group or the experimental group, which received a 12-week intervention. The program, primarily developed based on the Behavior Change Wheel (BCW) theory, offers health education on exercise, diet, BP monitoring, and medicine adherence (MA). It also includes other behavior interventions guided by an intervention manual, incorporating behavior change techniques (BCTs). The primary outcomes encompass BP and adherence indicators, while the secondary outcomes encompass cardiovascular function indicators, body composition indicators, learning performance, satisfaction, and acceptability. The exercise and blood pressure monitoring adherence (BPMA) indicators for the WHBDIP group were assessed weekly via WeChat during the initial 3 months, while other outcome data for both groups will be collected at the baseline assessment phase, 3 months after the intervention, and 1 year after the program.

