### Outcomes

#### Primary Outcomes

BP will be measured using a cardiovascular function monitor (BX-CFTI-100, Institute of Intelligent Machines) at 3 time points: the first baseline assessment phase (T0), the 12-week end point assessments phase (T1), and the end of the 1-year program (T2). The assessment details have been published elsewhere [32].

Exercise adherence (EA), DA, MA, and BPMA indicators were collected once a week through WeChat for the intervention group until T1. The BPMA will also be collected at T0, T1, and T2 for the control group. The exercise adherence indicator was calculated as the ratio of actual exercise time that meets the prescription's recommended intensity to the total time of the prescription-recommended intensity. PAT will be measured as an indicator by questioning subjects in both groups at T0, T1, and T2 about the type, duration (in minutes), and frequency (per week). It will be measured using the minutes or metabolic equivalent per week. The MA indicator will be measured at T0, T1, and T2 for both groups using the Modified Morisky Scale (Chinese version-MMS-8, Certificate Number: 8538-1877-1559-6025-5310) [34-36], which includes 8 simple questions. The rating is “poor medication adherence” for a final total score of <6 points, “moderate medication adherence” for a score of 6-7, and “good medication adherence” for a score of 8. Dietary adherence (DA) will be assessed at T1 and T2 for both groups based on their compliance with the “types of diet” and the “recommended amount of diet” (3 response levels for each question).

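### The medication-adherence comparison between arms makes no use of the baseline score, and if the three-level rating is tested, the named tests also ignore its order

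*Protocol article*

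**What the plan says.** The Methods part of the Abstract states: "The primary outcomes encompass BP and adherence indicators". Under Primary Outcomes, "The MA indicator will be measured at T0, T1, and T2 for both groups using the Modified Morisky Scale", an eight-question instrument. The same paragraph then turns the total into a rating: poor "for a final total score of <6 points", moderate "for a score of 6-7", and good for 8. Dietary adherence (DA) is assessed in both groups at T1 and T2, with three response levels per question.

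The Statistical Analysis section names four tests. Between groups, at each of three time points, it lists independent-samples t tests and, in the same sentence, says that "chi-square tests will be conducted to assess the significance of differences in baseline characteristics or outcomes". Over time it lists paired t tests and says that "McNemar's test will be used to compare the differences in some outcomes before and after the 3-month intervention", and likewise from before the trial to the end of the program. It names no rank or ordinal method and no adjustment for baseline, and it does not match individual outcomes to tests.

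**The concern.** MA is a primary outcome measured before and after in both arms, so the comparison between arms could use each participant's starting value. None of the between-arm tests named does this. The paired tests use the T0 value, but only for change over time, which does not compare the arms.

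A second loss depends on which form of MA is tested. MA is the only outcome in the article that has both explicit categories and repeated measurement from T0 in both arms, so it is a natural candidate for the categorical tests. Those tests suit it poorly. Pearson chi-square would give the same result if poor, moderate and good were relabelled in any order, and the standard McNemar's test is for paired two-level data. Three-level DA responses meet the same chi-square problem at T1 and T2.

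At stake is sensitivity. The trial has 68 participants and was sized on blood pressure (BP) alone. A real gain in medication adherence could be reported as no difference because the test left information unused.

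**Working it through.** **Inputs from the article.** Cut points <6, 6-7 and 8 (Primary Outcomes). N = 68, effect size 0.7 for BP, α = .05, β = .2 and attrition up to 20% (Sample Size).

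**Assumptions.** Equal arms, so 68/2 = 34 per arm, and 34 × 0.8 = 27.2, about 27 per arm after attrition. Two-sided .05. A 0.7 SD shift in adherence, borrowed from the BP planning figure because no MA effect is given.

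**The plan's own figure.** Per arm, n = 2(z₁ + z₂)²/0.7².
- Two-sided: 2(1.960 + 0.842)²/0.49 ≈ 32.0, so 33 per arm; the exact t test needs 34 per arm, or 68 in total, before attrition.
- One-sided: 2(1.645 + 0.842)²/0.49 ≈ 25.2, so 26 per arm; 26/0.8 = 32.5, so 33 per arm and 66 in total after attrition.

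So 68 is close to the one-sided figure with attrition, or equal to the two-sided figure without it. That is a separate matter from this point. It matters here only because 34 and 27 per arm are the sizes to examine.

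**Analytic check.** With n per arm, control proportions p₀, intervention proportions p₁ and their mean p̄, the chi-square test on 2 df has noncentrality λ = n Σ[(p₀ − p̄)² + (p₁ − p̄)²]/p̄. With control levels 0.40/0.40/0.20, a 0.7 SD shift gives 0.17/0.39/0.44, and the sum is about 0.183.
- 34 per arm: λ ≈ 6.2, power 0.61. Across three control splits the range is 0.59-0.61. A t test on a continuous score has 0.81.
- 27 per arm: λ ≈ 4.9, power 0.50. Across the three splits the range is 0.49-0.50. The t test has 0.71.

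**Simulation with a 0-8 integer score.** Normal scores with SD 1.5 and a shift of 0.7 × 1.5 = 1.05 were rounded, limited to 0-8 and cut at 6 and 8; 3,000 trials per row. The control means are assumptions.

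| Per arm | Control mean | t test, score | Mann-Whitney, score | Rank test, 3 levels | Chi-square, 3 levels |
|---|---|---|---|---|---|
| 34 | 5.0 | 0.792 | 0.772 | 0.671 | 0.565 |
| 34 | 5.5 | 0.788 | 0.775 | 0.709 | 0.597 |
| 34 | 6.0 | 0.771 | 0.766 | 0.729 | 0.622 |
| 34 | 6.5 | 0.761 | 0.751 | 0.719 | 0.611 |
| 27 | 5.0 | 0.686 | 0.666 | 0.572 | 0.467 |
| 27 | 5.5 | 0.694 | 0.680 | 0.612 | 0.505 |
| 27 | 6.0 | 0.681 | 0.671 | 0.629 | 0.535 |
| 27 | 6.5 | 0.644 | 0.631 | 0.610 | 0.501 |

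**Where the loss arises.**
- Total, t test minus chi-square: from 0.644 − 0.501 = 0.143 to 0.792 − 0.565 = 0.227.
- Grouping, Mann-Whitney on the score minus rank test on the levels: from 0.631 − 0.610 = 0.021 to 0.772 − 0.671 = 0.101.
- Ignoring order, rank test minus chi-square on the same levels: from 0.629 − 0.535 = 0.094 to 0.709 − 0.597 = 0.112.

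In every row the loss from ignoring order is at least as large as the loss from grouping.

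**Baseline.** In a linear model with T0 as covariate, the residual variance of the follow-up score is multiplied by about 1 − ρ², where ρ is the within-arm correlation between T0 and follow-up. The article gives no ρ, so no figure is put on this gain. It applies whichever form of MA the plan intends.

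**The case against.** The strongest reply is that the article assigns no outcome to any test. The t test stands in the same sentence as chi-square, and MMS-8 has a total score. That score could go to the t and paired t tests, with the rating shown only as counts and percentages. Matching outcomes to tests is commonly left to the analysis plan. This stands. A reader might infer that the plan cuts the score into groups in order to apply chi-square and McNemar's test, but the text does not say so.

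Three further points stand:
- McNemar's test is limited to some outcomes, and MA is not named among them. The scale of BP-monitoring adherence is not stated, so a binary outcome cannot be ruled out. A reader might conclude that the test has no place in the plan; the article does not support that. An extension for larger square tables also exists, although the article does not name it and it ignores order too.
- DA has no T0 value, but no before-after test is promised for it, so there is no contradiction.
- Pearson chi-square on three levels is a valid test between arms. The objection is to its efficiency. The trial was sized on BP, so no stated power claim for MA is broken.

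The reply does not restore the unused T0 score. Even on its favourable reading, the between-arm comparison is an unadjusted t test. Nor does it supply a method for ordered three-level responses, since none is named.

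**Conclusion.** The point holds in a conditional form. Without condition: as the tests are named, the comparison of arms on MA makes no use of the T0 score, and the article leaves open whether the score or the rating is tested. On condition that the rating is tested: chi-square ignores its order, and the standard McNemar's test does not fit it.

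Under that condition the illustrative loss against a t test on the score is about 14 to 23 percentage points. At 34 per arm power falls from 0.76-0.79 to 0.57-0.62, with 0.67-0.73 for a rank test on the levels. At 27 per arm it falls from 0.64-0.69 to 0.47-0.54, with 0.57-0.63 for the rank test. These figures rest on an assumed 0.7 SD shift, assumed score distributions, equal arms and two-sided .05. They show direction and rough size and do not predict this trial's power. It would be tempting to blame the grouping for most of the loss, but ignoring order accounts for at least as much.

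**What to change.** - Name the MMS-8 total score as the MA analysis variable. Compare arms at T1 and T2 with a model adjusted for the T0 score: linear, or proportional-odds if scores pile up at 8.
- Report the poor, moderate and good rating descriptively.
- Compare three-level DA responses between arms at T1 and T2 with an ordinal or rank test in place of chi-square.
- Restrict McNemar's test to any outcome defined as binary, and name that outcome.

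The cost is analysis wording only. MMS-8 is already scheduled at T0, T1 and T2 in both groups, so no new data are needed. The article's Results section places the start of analysis in August 2023 and the 1-year collection in September 2023. The wording should be fixed before the outcome comparisons are run.

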Digital health (such as mobile health [mHealth] or telehealth) intervention strategies have been used to improve hypertension management outside the hospital. These strategies enhance patient adherence behaviors and increase the feasibility of delivering convenient, continued health interventions in primary health care settings with unequal resource distribution and understaffing. Several recent meta-analyses have demonstrated that using an internet-based interactive intervention mode combining health information with decision support via a computer or mobile phone could lead to a reduction of mean SBP by 2.23-3.74 mm Hg and mean DBP by 1.14-2.99 mm Hg [16-18]. Most of the interventions conducted by the investigators aimed to influence “self-management” or “adherence behaviors” in patients with hypertension [16-18]. Another systematic review of the literature showed the improvement of patient adherence after mHealth intervention [12,17,19-21].

WeChat, a mobile app, is the most prevalent social communication tool in China, with over 1 billion monthly active users of all ages. Approximately 902 million users log into WeChat every day [22]. A substantial amount of prior research in health promotion has focused on WeChat-based programs, which have demonstrated high acceptability, feasibility, and efficacy [23]. WeChat-based health interventions have been found to increase adherence and willingness to seek treatment, improve follow-up rates, enhance health outcomes, quality of life, and self-care ability, and also promote patient satisfaction [23-28]. For hypertension management, WeChat-based programs showed improvements in BP monitoring, diet, self-efficacy, and self-management scores [29,30]. However, the effect of lowering BP is inconsistent. One study reported a significant improvement in BP (SBP: –6.9 and DBP: –3.1 mm Hg) between the intervention and control groups [30], while another study showed no statistical differences between the 2 groups [31]. Therefore, we aim to assess the effectiveness of the WeChat-based health behavioral digital intervention program (WHBDIP) in 2 groups after 3 months of intervention and at the end of an extended additional 7 months. This program involves exercise, diet, BP monitoring, and medication adherence intervention strategies. Our plan is to investigate whether this approach is accessible and effective in improving outcomes for older individuals with hypertension.

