### Sample Size

The sample size was calculated based on the primary outcome of BP. The effect size, widely used to measure treatment effects of continuous outcomes, is calculated as the difference between groups divided by the pooled SD. A previous meta-analysis, comparing mHealth intervention treatments with other traditional treatments, with the primary outcome being BP, reported an effect size of 0.7 [17]. Assuming α=.05, β=.2, and accounting for up to 20% attrition, a sample size of 68 is needed for this study.

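### The T1 and T2 between-arm t tests leave out baseline blood pressure, which costs precision and leaves a chance baseline gap uncorrected

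*Protocol article*

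**What the plan says.** Under Primary Outcomes, BP is taken with one cardiovascular function monitor "at 3 time points: the first baseline assessment phase (T0), the 12-week end point assessments phase (T1), and the end of the 1-year program (T2"). A baseline value from the same device is therefore planned for every patient.

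Under Statistical Analysis, chi-square tests and independent-samples t tests "will be conducted to assess the significance of differences in baseline characteristics or outcomes between the control group and intervention group", separately at three times, the first of them before the intervention starts. The only other use of T0 is in paired t tests and McNemar's test for before-after differences, which do not compare the arms. The section names no baseline covariate, no between-arm comparison of change and no repeated-measures model. It gives no rule for what follows a significant or non-significant baseline test.

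Under Sample Size, the design effect is 0.7 for BP, where an effect size "is calculated as the difference between groups divided by the pooled SD". The section concludes: "Assuming α=.05, β=.2, and accounting for up to 20% attrition, a sample size of 68 is needed for this study".

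**The concern.** Testing baseline differences after randomisation examines a null hypothesis that is true by design, so the result says little about whether the follow-up comparison needs adjustment. What matters is how strongly baseline BP predicts follow-up BP.

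The T1 and T2 tests carry two things that the T0 value could remove. One is the stable variation in BP between patients, which widens the standard error. The other is the chance baseline gap in the single randomisation that the trial has, which moves the observed follow-up difference by r times that gap. In a trial of 68 patients both can be material. The analysis is stated outright in the article, so this is a choice that the plan makes and not a detail left to a separate analysis plan.

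**Working it through.** **Inputs from the article.** Effect 0.7 SD, α = .05, power 80%, attrition up to 20% and N = 68 (Sample Size); three BP visits (Primary Outcomes); separate t tests at each visit (Statistical Analysis).

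**Assumptions not in the article.** Allocation of 34 per arm; two-sided tests; a T0-to-follow-up correlation r of 0.3 to 0.7, the same in both arms; the 0.7 standardised by the SD of follow-up values. Where mm Hg are shown, an SBP SD of 12 to 18.

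**1. The plan's own figure.** By noncentral t, a two-sided t test at d = 0.7 needs 34 per arm, or 68 in total, for 80% power (exact power 81.2%). This matches 68, but with no attrition allowance: 68/0.8 = 85. With 20% lost, 34 × 0.8 = 27.2, so about 27 per arm remain and power is 71.4%. The missing allowance is a separate matter; it is used here only to set the two scenarios.

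**2. Largest T0 gap that is non-significant.** The limit is t(.975, 2n−2) × √(2/n).
- n = 34: √(2/34) = 0.2425 and the limit is 0.484 SD. Against the design effect, 0.484/0.7 = 69%.
- At an SD of 12, 15 or 18 mm Hg, the limit is 5.8, 7.3 or 8.7 mm Hg. The design effect on the same scale is 8.4, 10.5 or 12.6 mm Hg.

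**3. Shift in the follow-up contrast.** Given a T0 gap, the expected difference under no treatment effect is r × gap. At the limit this is 0.3 × 0.484 = 0.15 SD up to 0.7 × 0.484 = 0.34 SD, or 21% to 48% of the design effect.

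**4. Precision and power.** ANCOVA multiplies the residual variance by 1 − r², so the standardised effect becomes 0.7/√(1 − r²), with one degree of freedom fewer (65 or 51).

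| r | variance factor | power, 34 per arm | power, 27 per arm |
|---|---|---|---|
| t test without T0 | 1.00 | 81.2% | 71.4% |
| 0.3 | 0.91 | 84.6% | 75.3% |
| 0.4 | 0.84 | 87.3% | 78.6% |
| 0.5 | 0.75 | 90.7% | 83.0% |
| 0.6 | 0.64 | 94.5% | 88.4% |
| 0.7 | 0.51 | 97.8% | 94.2% |

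**5. Error rate, both sides of the picture.** Take a gap of 0.4 SD, r = 0.6 and 34 per arm. The null follow-up difference has mean 0.6 × 0.4 = 0.24 SD and standard deviation √(1 − 0.36) × 0.2425 = 0.194 SD. Rejection in the direction of the gap then has probability 1 − Φ((0.484 − 0.24)/0.194), about 10%, against a nominal 2.5%. A gap of 0.4 SD or more, in either direction, arises in about 10% of randomisations: 2 × (1 − Φ(0.4/0.2425)). With no gap and the same r, the same test rejects only 2 × (1 − Φ(0.484/0.194)), about 1.3%, two-sided. These cases average out to 5%.

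**The case against.** The strongest reply is that the planned t test is valid. Its 5% error rate holds over randomisations, and with 34 per arm it reaches the stated 80% power. This stands, and the point is therefore one of efficiency and of exposure to the imbalance actually drawn. The 10% rejection rate in step 5 depends on an unusual gap and an assumed r, and must not be read as the test's error rate.

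A reader might infer that baseline gaps larger than the effect sought could go undetected. The article does not support this. The effect sought is 0.7 SD, the T0 test would flag anything above 0.48 SD, and a chance gap beyond 0.7 SD has a probability of about 0.4%. The inference works only if the effect sought is replaced by the background meta-analytic range in the Introduction ("could lead to a reduction of mean SBP by 2.23-3.74 mm Hg"), which the sample size does not use.

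A reader might also infer that a non-significant T0 test will be taken as proof of balance. The Statistical Analysis section states no such rule.

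Two further objections stand in part. The size of the gain rests wholly on an assumed r: at 0.3, power with 34 per arm rises only from 81.2% to 84.6%. And the 71% starting point with 27 per arm comes from the attrition allowance, not from the choice of test. Neither removes the gain, which is present throughout the assumed range in both scenarios.

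**Conclusion.** The point holds as a loss of precision and as an uncorrected chance imbalance, not as an invalid test. At r of 0.3 to 0.7, leaving T0 out gives up 9% to 49% of the variance. At d = 0.7 that is the difference between 81% and 85%-98% power with 34 per arm, and between 71% and 75%-94% with 27 per arm. A T0 gap of up to 0.48 SD would be non-significant and could move the follow-up contrast by up to 21% to 48% of the design effect. The 0.48 SD limit needs only 34 per arm and a two-sided .05 test. The shift and the power gains also rest on the assumed r, and the gains on reading 0.7 as standardised by the follow-up SD. The change is worth making because the covariate is already collected.

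**What to change.** In Statistical Analysis, replace the T1 and T2 between-arm t tests by ANCOVA: the outcome at the visit regressed on arm and the patient's own T0 value. Apply it to SBP and DBP and to other clearly continuous outcomes with T0 values in both arms, namely cardiovascular function, body composition and physical activity time. Report the adjusted difference with its 95% CI. Describe baseline characteristics by arm without P values.

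The medication adherence scale is graded into three categories, and the scoring of the self-made learning questionnaire is not described, so neither should be swept into this model by default.

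The article reports that 3-month data collection was completed in January 2023, so the change follows the collection of T1 data. Record it as a dated amendment before the analysis scheduled for August 2023, and state whether T1 results by arm had been seen. The cost is one degree of freedom and a documented change of analysis. No new data are needed.

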## Methods

### Trial Design and Setting

This is a 2-arm, parallel-group, randomized trial that includes a WeChat-based health behavioral digital intervention lasting for 12 weeks. The trial has been conducted at 2 community health centers, both located in Anhui province—1 in Hefei and the other in Bengbu. The primary data collection and evaluation will take place at 3 time points: the beginning of the project, after 3 months of intervention, and 1 year after the project starts.

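### Baseline BP is measured in both arms but left out of the between-arm comparison: the planned t tests are valid but give up precision that adjustment would recover at almost no cost

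*Protocol article*

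**What the plan says.** The Statistical Analysis section names the between-arm method outright: independent-samples t tests and chi-square tests "to assess the significance of differences in baseline characteristics or outcomes between the control group and intervention group at 3 time points", namely at baseline, at 12 weeks and at 1 year. It mentions no covariate, no between-arm comparison of change and no repeated-measures model.

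It also plans paired t tests and McNemar's test, which "will be used to compare the differences in some outcomes before and after the 3-month intervention" and again from before the trial to the end of the program. It does not say whether BP is among those outcomes.

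Primary Outcomes schedules BP at "the first baseline assessment phase (T0), the 12-week end point assessments phase (T1), and the end of the 1-year program (T2"), so a baseline BP exists by design. The Randomization section describes one list of 68 random numbers, with no stratification or balancing on BP. Not every outcome has the same schedule. In Primary Outcomes, "Dietary adherence (DA) will be assessed at T1 and T2 for both groups", with no T0 assessment stated. In Secondary Outcomes, learning performance is assessed at T0 and T1 only.

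**The concern.** A participant's BP before treatment usually predicts BP afterwards. If the arm comparison at T1 or T2 ignores it, the variation it could explain stays in the error term, and part of any chance difference between arms at T0 stays in the estimated effect. Neither planned use of the T0 value changes this. A significance test at baseline only describes imbalance that arose by chance. A paired before/after test does not compare the arms.

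The point matters here because the trial is small, recruitment is complete (Results), and the Introduction describes earlier WeChat findings on BP as inconsistent. The analysis is the main remaining means of sharpening the estimate.

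**Working it through.** **Inputs.** From Sample Size: effect size d = 0.7 (difference divided by pooled SD), alpha .05, beta .2, up to 20% attrition, total 68. Assumed because not stated: two-sided testing, 34:34 allocation, and r between baseline and follow-up from 0.3 to 0.7, with the same range used for T1 and T2.

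**The plan's own figure.** Without a covariate, n per arm = 2(z₁ + z₂)²/d².
- Two-sided: 2(1.960 + 0.842)²/0.49 = 32.04, so 33 per arm by the normal formula and 34 per arm (68 in total) by the exact t calculation, before attrition.
- One-sided: 2(1.645 + 0.842)²/0.49 = 25.2, so 26 per arm; 26/0.8 = 32.5, so 33 per arm and 66 in total after attrition.

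So 68 matches the two-sided number with no attrition allowance, or lies within 2 of the one-sided number with it. Either way it is a calculation without baseline adjustment.

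**Effect of adjustment.** Adjusting for baseline multiplies the residual SD by √(1 − r²). Power comes from the noncentral t with noncentrality d√(n/2)/√(1 − r²), on 2n − 2 df unadjusted and 2n − 3 df adjusted. After 20% attrition, 68 × 0.8 = 54.4, so 27 per arm.
- 27 per arm, unadjusted: 0.7 × √13.5 = 2.57.
- 34 per arm, unadjusted: 0.7 × √17 = 2.89.

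| r (assumed) | SE factor | Variance cut (r²) | Noncentrality, power at 27 per arm | Noncentrality, power at 34 per arm |
|---|---|---|---|---|
| none (t test) | 1 | 0 | 2.57, 71% | 2.89, 81% |
| 0.3 | 0.95 | 9% | 2.70, 75% | 3.03, 85% |
| 0.5 | 0.87 | 25% | 2.97, 83% | 3.33, 91% |
| 0.7 | 0.71 | 49% | 3.60, 94% | 4.04, 98% |

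At 27 per arm, adjusted power is 79% at r = 0.4, so 80% is reached between r = 0.4 and r = 0.5.

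**The same cost seen as imbalance.** The chance baseline difference has SE √(2/n) in SD units: √(2/34) = 0.24, or √(2/27) = 0.27. The unadjusted follow-up difference carries r times whatever imbalance occurs. At 34 per arm, an imbalance of one SE shifts it by 0.07, 0.12 or 0.17 SD at r = 0.3, 0.5 or 0.7, which is 10%, 17% or 24% of the planned 0.7. A gap above 0.3 SD has probability 0.22 (0.3/0.243 = 1.24 SE). It shifts the estimate by at least 0.3r, that is 0.09 SD at r = 0.3 and 0.21 SD at r = 0.7.

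This does not add to the loss of precision. The unadjusted variance 2/n splits into (1 − r²)(2/n), which adjustment leaves, and r²(2/n), which is the variance of r times the baseline difference.

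**Change scores are not an equivalent remedy.** Their variance factor is 2(1 − r), which exceeds 1 when r < 0.5. By the normal approximation with 54 completers, power is 59%, 73% and 91% at r = 0.3, 0.5 and 0.7, against 73% for the unadjusted comparison on the same approximation.

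**The case against.** The strongest reply is that nothing planned here is invalid. Under randomisation the t test keeps its type I error and is unbiased over repeated randomisations, and its standard error already allows for chance baseline variation. That stands. A reader might infer that the planned estimate is biased or the test wrong. It is not: any bias is conditional on the imbalance that happens to occur.

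The size of the gain also rests on an r that the document does not give. At r = 0.3 the gain is four percentage points of power, and the 1-year correlation could differ from the 12-week one. This too stands, and is why a range is shown.

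Four further readings go beyond the text:
- That T0 values serve only a baseline significance test. The paired tests also use them.
- That participants missing at a visit will be dropped. The article states no rule for missing data, and a fuller plan may.
- That leaving centre out is an error. "The trial has been conducted at 2 community health centers", but no stratification by centre is described, so adjusting for it is optional.
- That the trial is necessarily short of power. That depends on sidedness and realised attrition, a separate sample-size question; with all 68 followed, the unadjusted two-sided test has 81%.

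Finally, an unseen analysis plan might contain an adjusted model. The article nevertheless states its between-arm method explicitly, so this is a stated choice and not a detail left out.

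**Conclusion.** The concern holds as one of efficiency, not validity. The stated between-arm analysis leaves out a baseline measurement that the trial collects by design. The gain from using it ranges from modest (r = 0.3) to large (r = 0.7). At no value in that range does adjustment lose power, because the one degree of freedom it spends costs almost nothing. The power figures rest on d = 0.7, two-sided testing and equal allocation, and the two columns bracket attrition from none to the full 20%. The change is advisable but not essential to a valid test. It applies only to outcomes with a baseline value in both arms.

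**What to change.** For BP and other continuous outcomes measured at T0, T1 and T2 in both arms, replace the per-visit t tests with a baseline-adjusted comparison. Two forms are acceptable:
- ANCOVA at each visit: follow-up value on arm and baseline value.
- One linear mixed model of the T1 and T2 values, with arm, visit, arm × visit, baseline and baseline × visit. Centre may be added.

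Report the adjusted arm difference at T1 and at T2 with its 95% CI. For learning performance (T0 and T1 only) use ANCOVA at T1. Dietary adherence has no stated T0 value and cannot be adjusted for its own baseline. Present baseline characteristics descriptively, without P values. Paired before/after results may still be shown, but not as evidence of a difference between arms.

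**Cost.** No new data and a few lines of SPSS syntax. Because the Results section puts completion of the 3-month data in January 2023, the change should be recorded as a dated amendment, with its reason, before any outcome is analysed by arm.
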